## Abstract

**Background:**

"Doing the month", or "sitting month", is a traditional practice for postpartum women in China and other Asian countries, which includes some taboos against well-accepted healthy diet and lifestyles in general population. Previous studies have shown this practice may be associated with higher prevalence of postpartum problems. The current multicenter randomized controlled trial (RCT) aims to evaluate outcomes of diet and lifestyle interventions in Chinese postpartum women.

**Methods/Design:**

The current multicenter RCT will be conducted in three representative areas in China, Shandong province, Hubei province and Guangdong province, which locate in northern, central and southern parts of China, respectively. Women who attend routine pregnancy diagnosis in hospitals or maternal healthcare centers will be invited to take part in this study. At least 800 women who meet our eligibility criteria will be recruited and randomly assigned to the intervention group (n > = 400) and the control group (n > = 400). A three-dimension comprehensive intervention strategy, which incorporates intervention measures simultaneously to individual postpartum woman, their family members and community environment, will be utilized to maximize the effectiveness of intervention. Regular visiting and follow-up will be done in both group; nutrition and health-related measurements will be assessed both before and after the intervention.

**Discussion:**

To our knowledge, this current study is the first and largest multicenter RCT which focus on the effectiveness of diet and lifestyle intervention on reducing the incidence rate of postpartum diseases and improving health status in postpartum women. We hypothesize that the intervention will reduce the incidence rates of postpartum diseases and improve nutrition and health status due to a balanced diet and reasonable lifestyle in comparison with the control condition. If so, the results of our study will provide especially important evidence for changes in both the concept and action of traditional postpartum practice in China.

**Trial Registration:**

ClinicalTrials.gov ID NCT01039051.

## Background

The postpartum period, or puerperium, which starts about an hour after the delivery of the placenta and includes the following six weeks, covers a critical transitional time for a woman, her newborn and her family, on a physiological, emotional and social level. However, the postpartum period is often neglected by maternity care in both developing and developed countries [1]. In addition, women's needs during this period have been all too often eclipsed by the attention given to pregnancy and birth [2]. The lack of postpartum care ignores the fact that the majority of maternal deaths and disabilities occur during the postpartum period and that early neonatal mortality remains high [3,4].

"Doing the month", or "sitting month", is a well-accepted and obeyed traditional practice among postpartum women and their families in China, which is also common in other Asian countries, such as Korea, Thailand, and Singapore [5-7]. According to traditional customs, women who are "doing the month" are advised to lie in bed all the time with doors and windows closed, and consume plenty of eggs or meat, drink bowels of chicken soup, brown sugar water, and millet gruel every day, while avoid eating any raw and cold food (mainly refers to fruits, vegetables), because cold food were thought to be unfavorable for postpartum recovery [8-10]. This practice seems to be believed more or less by almost all Chinese population worldwide, rather than only by local people in China mainland. Immigration studies showed that Chinese women who immigrated to Australia, Canada or United States still think that the traditional puerperium practice of "doing the month" is very important, and this belief is not subject to their level of education, acculturation level and the duration of immigration [11-14].

We have ever conducted a preliminary study in three regions of Hubei province in China to investigate prevalence of puerperium practice and their effect on postpartum women's health [15,16]. We found that 18% of women never ate vegetables, 78.8% never ate fruit and 75.7% never drank milk during the puerperium while, in contrast, the consumption of eggs and brown sugar were as high as 365.0 g/d and 81.3 g/d in rural postpartum women, which is associated with postpartum problems including constipation, backaches, breast problems, oral diseases and anemia, et al [15].

However, as indicated in a Cochrane systematic review [17], evidence is too limited at present to confirm the effect of diet and lifestyle modification on outcomes for the postpartum women and their offspring. Therefore, we initiate this multicenter randomized controlled trial (RCT) with large-scale sample size to elucidate whether a diet and lifestyle intervention can improve the health status in Chinese postpartum women.

## Methods/Design

### Objectives

This multicenter RCT is designed to assess the effectiveness of a diet and lifestyle intervention in postpartum women in China, including a short-term effect on reducing health problems during puerperium period and a long-term effect on improving health status in women and their offspring over a two-year period.

### Study Population

The current multicenter study will be conducted in three representative areas in China, Shandong province, Hubei province and Guangdong province, which locate in northern, central and southern parts of China, respectively. Women who attend routine pregnancy diagnosis in hospitals or maternal healthcare centers will be invited to take part in the randomized controlled intervention trial.

### Sample size

Sample size has been calculated as the following formula [18]:

, in which *p*_*1 *_indicates incidence rate in control group, *p*_*2 *_indicates incidence rate in intervention group and  indicates average of *p*_*1 *_and *p*_*2*_. Z_α/2 _is 1.96 when significance level (α) is 0.05 and Z_β _is 1.64 for power (1 - β) is 0.90.

Take constipation, a typical diet-related digestive disorder, for example. The incidence rate of constipation in our previous study is 20.95% in the control group [16]. We aim to reduce the incidence rate by 50%, which is 10.475%, the sample size N = = 309.89 ≈ 310 for each group. On the basis of the above calculation, a sample size of 800 participants (400 in the intervention group and 400 in the control group) has been determined, considering a certain attrition rate. This sample size is adequate, with statistical power >80%, for nearly all the major outcomes, including changes in nutritional status and health status.

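### The sample-size paragraph pairs Z_β = 1.64 with 90% power, but 1.64 is the 95% value; the 310 per group belongs to 95% power (a conservative mislabel and a minor correction)

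*Protocol article*

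**What the plan says.** All of the relevant text is in the Sample size section under Methods/Design of the protocol article.

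- Significance level: Z_α/2 "is 1.96 when significance level (α) is 0.05".
- Power: Z_β "is 1.64 for power (1 - β) is 0.90".
- Control rate: "The incidence rate of constipation in our previous study is 20.95% in the control group".
- Target: "We aim to reduce the incidence rate by 50%, which is 10.475" per cent in the intervention group.
- Result: "309.89 ≈ 310 for each group".
- Planned size: 800 women, "400 in the intervention group and 400 in the control group", reached from the 310 by "considering a certain attrition rate". No percentage is attached.
- General claim for the planned size: it is adequate "with statistical power >80%, for nearly all the major outcomes".

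Constipation is introduced as an example. The Outcome measurements section names knowledge and belief as the primary outcome and lists constipation among the postpartum diseases under the tertiary outcome. Nothing elsewhere in the article explains or corrects the pairing of 1.64 with 0.90.

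**The concern.** In a sample-size formula Z_β is the one-sided standard normal quantile at the stated power. For power 0.90 that is 1.28. The value 1.64 is the quantile at 0.95. The sentence is therefore wrong as it stands, and either the power or the quantile has to change.

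This is the only worked derivation behind the 800 women. If 1.64 were a misprint for 1.28 and the arithmetic had used 1.28, only the printed quantile would need changing. If 1.64 was used, the stated power and the stated number per group do not belong together, and a reader who repeats the calculation at 90% power will not obtain 310. The check below settles which of the two happened and in which direction the error runs.

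**Working it through.** **Inputs** (all from the Sample size section): p1 = 0.2095; p2 = 0.10475; Z_α/2 = 1.96; Z_β = 1.64, labelled as power 0.90; equal groups.

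**Formula.** The formula itself is missing from the text at hand. The section defines p1, p2 and their average, which points to the two-proportion formula with pooled variance under the null and unpooled variance under the alternative:

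n per group = [Z_α/2 · √(2·p̄(1 − p̄)) + Z_β · √(p1(1 − p1) + p2(1 − p2))]² / (p1 − p2)²

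This is an inference, tested in the first two steps.

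**Step 1: reproduce the printed figure.**
- p̄ = (0.2095 + 0.10475)/2 = 0.157125
- √(2 × 0.157125 × 0.842875) = √0.264873 = 0.51466
- √(0.2095 × 0.7905 + 0.10475 × 0.89525) = √0.259387 = 0.50930
- (p1 − p2)² = 0.10475² = 0.0109726
- Numerator with Z_β = 1.64: (1.96 × 0.51466 + 1.64 × 0.50930)² = (1.00873 + 0.83525)² = 3.4003
- n = 3.4003 / 0.0109726 = 309.89

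This agrees with the article to two decimals.

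**Step 2: can another formula reach 310 at 90% power?**

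| Form | Z_β = 1.64 | Z_β = 1.28 |
|---|---|---|
| Pooled under null, unpooled under alternative | 309.89 | 251.33 |
| Fully pooled | 312.85 | 253.41 |
| Fully unpooled | 306.37 | 248.16 |
| Arcsine | 304.69 | 246.80 |
| First form with continuity correction | 328.70 | 270.08 |

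Only the first form with 1.64 gives 309.89. No form with 1.28 comes near 310; the highest is 270.08. A one-sided 5% test at 90% power (1.645 and 1.28) would need only 204.65. So 1.64 was the value used.

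**Step 3: which power goes with 1.64?** Φ(1.64) = 0.9495 and Φ(1.28) = 0.8997. The exact quantiles are 1.2816 for 0.90 and 1.6449 for 0.95.

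**Step 4: the number per group at 90% power.** With Z_β = 1.28: (1.00873 + 1.28 × 0.50930)² / 0.0109726 = 251.33. With 1.2816 it is 251.57. Both round up to 252, which is 58 fewer than 310 (58/310 = 18.7%).

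**Step 5: power at the article's numbers**, from Φ[(0.10475·√n − 1.00873)/0.50930]:

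| n per group | Power |
|---|---|
| 251 | 0.899 |
| 310 | 0.950 |
| 400 (no attrition) | 0.984 |

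**Context: room for attrition in 400 per group.** Counting from 310, 1 − 310/400 = 22.5%. Counting from 252, 1 − 252/400 = 37%. The article states neither figure.

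**The case against.** The strongest reply is that the slip is harmless. It asks for more women than 90% power needs, the target of 400 per group stays as it is, and for this example power remains at or above 90% until fewer than 252 women per group are left. No analysis or error rate depends on it. All of that stands, and it is why the point is a minor correction.

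A second reply is that 1.64 does correspond to 0.90 if β is split over two tails (1 − 0.10/2 = 0.95). The article's own notation does not support this: it halves α but not β, and power in this formula is one-sided in β.

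Three stronger readings are tempting, and the documents support none of them.

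- *The trial is wrongly powered.* A reader might infer this from a wrong power statement. The error runs the other way, and the 0.90 is the design power of one worked example, not of the primary outcome.
- *The general claim of more than 80% power is false.* This error does not touch that claim. Constipation exceeds it at 310 and at 400, and the formula in Step 5 still gives about 82% at 200 per group.
- *The attrition allowance has been misjudged.* The article prints no attrition percentage, so no stated margin is contradicted. The 22.5% and 37% are back-calculations. A condensed article may also leave the figure to the full protocol, so its absence is not an error.

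It is also fair to say that the formula had to be inferred. The match to two decimals, together with the failure of the other forms, makes the inference strong.

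**Conclusion.** The point holds as a definite but conservative arithmetic error. The article's power label (0.90) and its sample size (310 per group) do not belong together: for 20.95% against 10.475% at two-sided 5%, 310 per group gives 95.0% power, and 90% power needs 252. The wrong pairing is in the calculation and not only in the printed text. At the planned 400 per group, power for this example is 98.4% before attrition.

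The consequence is a misreported design power for one illustrative outcome. Power is not lost and enrolment does not change. The conclusion assumes the inferred formula, the normal approximation without continuity correction, individual allocation in equal groups, and the article's own two rates. The identification of 1.64 as the 95% quantile depends on none of these.

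**What to change.** Keep 400 per group and correct the one sentence in the Sample size section. Because 1.64 was used in the calculation, the simplest correction changes only the label: power (1 − β) = 0.95 with Z_β = 1.64, giving 310 per group. This leaves the printed 309.89 and the step to 400 as they are. (The less rounded 1.645 gives 310.75, that is 311, a trivial difference.)

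If 90% power was what the design intended, write Z_β = 1.28 and 252 per group instead. That replaces the printed result and leaves 400 resting on a wider margin that the article does not describe, so it is the less tidy choice.

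Either way the cost is a one-line edit, with no change to recruitment, randomization or analysis.

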### Recruitment process

The flowchart of participant's recruitment process and trial design is summarized in figure 1. Pregnancy women that are willing to take part in our study will be checked by our eligibility criteria. The eligibility criteria for enrollment includes: 1) healthy pregnant women; 2) at their third trimester; 3) had at least three routine examinations at these antenatal clinics [16]. A written consent form will be assigned by each woman to confirm her willingness to participate, and then baseline data will be collected by a questionnaire survey (main components shown in Table 1) and a consequent anthropometric measurement.

**Table 1 T1:** Overview of the Questionnaires

Categories	Items
General information	Age, residence, occupation, education level, family economic situation, height, body weight, diagnosis of diseases, family history of diseases

Basic knowledge in nutrition and health	- Food guide pyramid knowledge - Nutrient-food association knowledge - Special nutritional requirement during postpartum period

Food intake	- Frequency and amount of cereals intake - Frequency and amount of vegetables intake - Frequency and amount of fruits intake - Frequency and amount of meat intake - Frequency and amount of eggs intake - Frequency and amount of milk and its products intake - Frequency and amount of soybean and its products intake - Frequency and amount of brown sugar intake - Frequency and amount of dietary oil intake - Frequency and amount of salt intake - Frequency and amount of other substance intake (alcohol, strong tea, coffee, et al.)

Health-related behaviors and Physical activities	Teeth brushing, Bathing and Hair washing Ventilation Always lie in the bed or Get up for wandering Maternal keep-fit exercises Light physical activity or Heavy physical activity Basking in the sun

**Table 2 T2:** Comparison between Traditional Practices for "Doing the Month" and Expected Diet and Lifestyle that We Advocated during the Postpartum Period

	Traditional practices for "doing the month"	Expected diet and lifestyle during the postpartum period
**Dietary Habits**	Eat plenty of food	Increase total amount of food in accordance with energy expenditure
	
	Meat-based diet components	Diverse food with both animal foods and plant-derived foods
	
	Eat "hot" or "Yang" food (referred to meat, sugar, eggs, chicken soup, et al)	Ensure sufficient protein intake from fish, poultry meat, lean meat and eggs Enjoy milk, soybeans, or their products daily Restrict fat intake from animal foods
	
	Avoid "cold" or "Yin" food (referred to fruit, vegetables, cold water, et al)	Eat more vegetables fruits and nuts in various species Drink sufficient quantity of water and juice every day Have liquid food, such as non-greasy soup, before or between meals
	
	Keep dietary taboos in mind	Advise the woman against dietary taboos about foods which are nutritionally healthy. Reassure the mother that she can eat any normal foods. Talk to family members such as husband and mother-in-law, to encourage them to help ensure the woman eats enough.
	
		Eat more foods rich in dietary fiber
	
		Supplement with vitamins and minerals
	
		Restrict salt consumption in diet
	
		Avoid drinking alcohol, strong tea or coffee

**Other Health-related behaviors**	Never brush teeth	Brush teeth twice per day
	
	Never bathe or wash hair	If possible, take a shower every day in a warm room and wash hair at least once a week
	
	Shut well all windows or doors all the time	Ventilate regularly, but avoiding the cold wind blowing directly to the mother and child
	
	Always lie in bed without any physical activity almost all day and night	Do maternal keep-fit exercises and increase physical activities gradually to maintain a healthy weight

**Figure 1 F1:**
[figure not shown]
**Flowchart of participant's recruitment and trial design**.

### Randomization

Recruited women will be randomly allocated to either intervention group or control group according to a random number generated by a computer-based procedure. Then, a unique code for each participating woman and her allocation will be recorded.

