### Statistical methods

Descriptive statistics will be calculated and checked for balance in intervention and control groups in demographic, health and outcome measurements at baseline. Comparisons between intervention group and control group will be performed by Chi-square (categorical variables), t test (continuous variables, normal distribution) or Mann-Whitney U test (continuous variables, skewed distribution). Final analyses will be undertaken using generalized linear mixed models to investigate changes over time in the two groups in the major outcomes. These models allow for repeated measures and can be used for normally distributed, binomial, and ordinal data [22]. All statistical analyses will be performed using SPSS 12.0 statistical software package (SPSS Inc, Chicago, IL, USA).

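### Randomization names no blocks or strata and the stated two-group tests pool three provinces; stratifying by province and adjusting for it is a minor, nearly free gain in precision

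*Protocol article*

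**What the plan says.** All references are to the protocol article.

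- **Randomization:** women are assigned to one of the two groups "according to a random number generated by a computer-based procedure". A unique code and the allocation are then recorded. No block, stratum or allocation ratio is given here.
- **Study Population:** the trial runs in "three representative areas in China, Shandong province, Hubei province and Guangdong province", "which locate in northern, central and southern parts of China, respectively".
- **Sample size:** 800 women, "400 in the intervention group and 400 in the control group". The abstract words the same targets as minimums, in total and per arm.
- **Statistical methods:** "Comparisons between intervention group and control group will be performed by Chi-square (categorical variables), t test" for normally distributed continuous variables, and Mann-Whitney for skewed ones. Province and site do not appear. Baseline balance will be checked. The final analysis is a generalized linear mixed model for change over time, whose fixed and random terms are not listed.

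**The concern.** Province is known for every woman when she is randomised, because she is recruited in one of three named provinces, and residence is among the baseline questionnaire items in Table 1. The Interventions section itself lists culture, social and economic conditions, education, family income and inherited custom as influences on puerperium belief and practice. The primary outcome is knowledge and belief, so it could plausibly vary by region. The preliminary data come from Hubei only, so levels in Shandong and Guangdong are unknown.

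If allocation is unrestricted and the arms are compared by pooled tests, two things follow. The arms can differ by chance in their mix of provinces. Any variation between provinces also stays in the error term, where it widens confidence intervals and lowers power. The stake is efficiency. It is not the validity of the comparison.

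**Working it through.** **1. The plan's own figure.** Inputs from Sample size: p1 = 0.2095, p2 = 0.10475, difference 0.10475, mean 0.157125, Z = 1.96 and 1.64.

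n = [1.96·√(2 × 0.157125 × 0.842875) + 1.64·√(0.2095 × 0.7905 + 0.10475 × 0.89525)]² / 0.10475² = (1.0087 + 0.8353)² / 0.010973 = 309.89.

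This reproduces the stated 310 per group. As a separate matter, Z = 1.64 belongs to 95% power, not to the stated 90%, which needs 1.28 and 252 per group. Constipation therefore has power to spare.

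**2. Overall split if allocation is unrestricted.** Binomial(800, 0.5) has SD √(800 × 0.25) = 14.1, a 95% range of 372 to 428, and a 2.8% chance of exactly 400/400. Power for constipation (variance pooled under the null) is 0.9835 at 400/400 and about 0.983 at 372/428. The loss is about 0.05 percentage points, which is immaterial.

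**3. Split within a province.** Assume equal thirds, 800/3 ≈ 267. Binomial(267, 0.5) gives a 95% range of 118 to 149 for one arm (44% to 56%).

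To see what this can do, assume control rates of 10%, 20.95% and 31.9% in the three provinces. Suppose one arm has 149 against 118 women in the highest-rate province and 118 against 149 in the lowest. The chance shift is 31 × (0.319 − 0.10)/400 = 1.7 percentage points, against a target difference of 10.475 points.

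**4. Variance removed by a province term, constipation.** The province rates are assumed, with mean 20.95%, and halved in the intervention arm. The share removed is the between-province variance summed over the two arms, divided by the total 0.16561 + 0.09378 = 0.25939. For rates of 16/20.95/25.9% the control part is 2 × 0.0495²/3 = 0.001634 and the intervention part is a quarter of that, so the share is 0.002042/0.25939 = 0.8%.

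Power = Φ(0.10475/√(0.25939 × (1 − share)/400) − 1.96), using the unpooled variance:

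| Assumed control rates | Share removed | Power without term | Power with term |
|---|---|---|---|
| 16 / 20.95 / 25.9% | 0.8% | 0.9844 | 0.9850 |
| 10 / 20.95 / 31.9% | 3.9% | 0.9844 | 0.9873 |
| 5 / 20.95 / 36.9% | 8.2% | 0.9844 | 0.9902 |

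**5. An outcome with 80% power.** The Sample size section claims only more than 80% power for nearly all major outcomes. With an assumed province share f, power = Φ((1.96 + 0.8416)/√(1 − f) − 1.96):

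- f = 5%: 2.8016/0.9747 − 1.96 = 0.914, power 82%
- f = 10%: 2.8016/0.9487 − 1.96 = 0.993, power 84%
- f = 20%: 2.8016/0.8944 − 1.96 = 1.172, power 88%

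**6. Validity without adjustment.** 40,000 trials were simulated per scenario, with 267/267/266 women, unrestricted allocation, no treatment effect, and either equal province rates or the three sets above. The unadjusted test rejected in 0.049 to 0.051 of trials, and a Mantel-Haenszel test stratified by province in 0.049 to 0.050.

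**The case against.** The strongest reply is that this reads silence in a condensed article as a design. A blocked or stratified list is also generated by computer from random numbers. Nothing in the Randomization section says that allocation is simple, and block and stratum details are often left to the full protocol. That stands: unrestricted allocation is an inference, so the point is conditional on the method being followed as written. Likewise the mixed model's terms are not listed, so a province term in the final analysis is not excluded. Only the chi-square, t and Mann-Whitney comparisons are shown to pool provinces.

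It can also be said that randomising 800 women without strata is sound practice. That is true, and it limits the point to an improvement on a valid method.

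Three stronger readings are tempting and are not supported:

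- **That the provinces were chosen because they differ.** The article calls them representative areas and gives no outcome rates by province. The Background describes the custom as held almost universally among Chinese people, and the Discussion names ethnic minorities as the source of varying practice. Separate intervention staff by province are not described either.
- **That missing exactly 400/400 matters.** It costs about 0.05 points of power, and targets worded as minimums can be met by recruiting somewhat beyond 800. About 860 women would give a better than 95% chance that both arms reach 400.
- **That province imbalance biases the result.** It is chance variation, which the unadjusted test already allows for, as the simulated type I error shows.

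**Conclusion.** The point holds as a minor, nearly free improvement. The stated allocation names no restriction, and the stated two-group tests ignore a factor that is known for every woman. If followed as written, inference stays valid. The cost is some precision and chance imbalance within provinces that could have been avoided.

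For constipation the gain is negligible to small, at most about 0.6 percentage points of power in the scenarios tried (0.9844 to 0.9902). For other outcomes it could be 2 to 8 points if power is 80% and province carries 5% to 20% of the variance. Those shares, the province rates and the equal province sizes are all assumptions, because the article gives no data by province.

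**What to change.** 1. In Randomization, state the method: 1:1 allocation in permuted blocks of randomly varying size, stratified by province (or by recruiting hospital). If the full protocol already specifies this, one sentence in the text is enough.
2. In Statistical methods, include province as a fixed effect in the mixed model for each outcome.
3. Replace the pooled chi-square, t and Mann-Whitney comparisons by province-adjusted ones: Mantel-Haenszel for binary tables, a model with province for continuous outcomes, and a stratified rank test for skewed ones.

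The allocation and analysis changes belong together, because stratified allocation analysed by pooled tests does not collect the gain in precision. The cost is one change to the allocation program and one model term. No extra women and no extra data are needed. If recruitment has already begun, the analysis changes can still be made before group assignment is revealed to the analysts.
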